## 6. Study Intervention(s) and Concomitant Therapy

Study intervention is defined as any investigational intervention(s), marketed product(s), placebo, or medical device(s) intended to be administered to a study participant according to the study protocol.

### 6.1. Study Intervention(s) Administered

| ARM Name                | Intervention                                                                                                | Control                                                                                                     |
|-------------------------|-------------------------------------------------------------------------------------------------------------|-------------------------------------------------------------------------------------------------------------|
| Intervention Name       | Metformin                                                                                                   | Placebo comparator                                                                                          |
| Type                    | Drug                                                                                                        | Drug                                                                                                        |
| Dose Formulation        | Film-coated tablet                                                                                          | Film-coated tablet                                                                                          |
| Unit Dose Strength(s)   | 850 mg                                                                                                      | N/A                                                                                                         |
| Dosage Level(s)         | One tablet once daily for 4 weeks, followed by one table twice daily                                        | One tablet once daily for 4 weeks, followed by one table twice daily                                        |
| Route of Administration | Oral                                                                                                        | Oral                                                                                                        |
| Use                     | Experimental                                                                                                | Placebo                                                                                                     |
| IMP and NIMP            | IMP                                                                                                         | IMP                                                                                                         |
| Sourcing                | Provided centrally by the trial site                                                                        | Provided centrally by the trial site                                                                        |
| Packaging and Labeling  | Study Intervention will be provided in boxes. Each box will be labeled as required per country requirement. | Study Intervention will be provided in boxes. Each box will be labeled as required per country requirement. |

### 6.2. Preparation/Handling/Storage/Accountability

1. The investigator or designee must confirm appropriate temperature conditions have been maintained during transit for all study intervention received and any discrepancies are reported and resolved before use of the study intervention.
2. Only participants enrolled in the study may receive study intervention and only authorized site staff may supply or administer study intervention. All study intervention

must be stored in a secure, environmentally controlled, and monitored (manual or automated) area in accordance with the labeled storage conditions with access limited to the investigator and authorized site staff.

3. The investigator, institution, or the head of the medical institution (where applicable) is responsible for study intervention accountability, reconciliation, and record maintenance (i.e., receipt, reconciliation, and final disposition records).
4. For all study sites, the local country Sponsor personnel or designee will provide appropriate documentation that must be completed for drug accountability and return, or local discard and destruction if appropriate. Where local discard and destruction is appropriate, the investigator is responsible for ensuring that a local discard/destruction procedure is documented.
5. The study site is responsible for recording the lot number, manufacturer, and expiry date for any locally purchased product (if applicable) as per local guidelines unless otherwise instructed by the Sponsor.

### 6.3. Measures to Minimize Bias: Randomization and Blinding

|                      |                                                                                                                                                                                                                                                                                                                                                                                                                                                                                                                                                                                                                                                                                                                                                                                                                                                                                                                                                                                                           |
|----------------------|-----------------------------------------------------------------------------------------------------------------------------------------------------------------------------------------------------------------------------------------------------------------------------------------------------------------------------------------------------------------------------------------------------------------------------------------------------------------------------------------------------------------------------------------------------------------------------------------------------------------------------------------------------------------------------------------------------------------------------------------------------------------------------------------------------------------------------------------------------------------------------------------------------------------------------------------------------------------------------------------------------------|
| Randomization | 
All participants will be centrally assigned to randomized study intervention using REDCap program. Before the study is initiated, the log in information and training the REDCap will be provided to investigators.
 
Study intervention will be dispensed at the study visits summarized in the SoA.
 
Returned study intervention should not be re-dispensed to the participants.
 
The randomization list will be generated using software SAS 9 for Windows. The randomization list will be imported into the REDCap program so the researchers can randomize candidate subjects using an easier-to-use interface. Subjects that meet the selection criteria will be randomized in a 1:1 ratio between the two treatment groups (Intervention arm: Metformin vs Control arm: placebo), stratifying by age in order to achieve balanced randomization in the two treatment groups. The assignment of treatment to each subject will be centralized, keeping the sequence hidden.
 |
|----------------------|-----------------------------------------------------------------------------------------------------------------------------------------------------------------------------------------------------------------------------------------------------------------------------------------------------------------------------------------------------------------------------------------------------------------------------------------------------------------------------------------------------------------------------------------------------------------------------------------------------------------------------------------------------------------------------------------------------------------------------------------------------------------------------------------------------------------------------------------------------------------------------------------------------------------------------------------------------------------------------------------------------------|

|                                                                                    |                                                                                                                                                                                                                                                                                                                                                                                                                                                                                                                                                                                                                                                                                                                                                                                                                                                                                                                |
|------------------------------------------------------------------------------------|----------------------------------------------------------------------------------------------------------------------------------------------------------------------------------------------------------------------------------------------------------------------------------------------------------------------------------------------------------------------------------------------------------------------------------------------------------------------------------------------------------------------------------------------------------------------------------------------------------------------------------------------------------------------------------------------------------------------------------------------------------------------------------------------------------------------------------------------------------------------------------------------------------------|
| Blind Break                                                                 | In case of an emergency, the investigator has the sole responsibility for determining if unblinding of a participants' intervention assignment is warranted. Participant safety must always be the first consideration in making such a determination. If the investigator decides that unblinding is warranted, the investigator should make every effort to contact the sponsor prior to unblinding a participant's intervention assignment unless this could delay emergency treatment of the participant. If a participant's intervention assignment is unblinded, the sponsor must be notified within 24 hours after breaking the blind. The date and reason that the blind was broken must be recorded in the source documentation.                                                                                                                                                                      |
| Blinded study with unblinded site pharmacist who is dispensing intervention | 
Participants will be randomly assigned in a [1:1] ratio to receive study intervention. Investigators will remain blinded to each participant's assigned study intervention throughout the course of the study. To maintain this blind, an otherwise uninvolved 3rd party will be responsible for the dispensation of all study intervention and will endeavor to ensure that there are no differences in time taken to dispense following randomization.
 
This 3rd party will instruct the participant or legally authorized representative to avoid discussing the taste, dosing frequency, or packaging of the study intervention with the investigator.
 
In the event of a Quality Assurance audit, the auditor(s) will be allowed access to unblinded study intervention records at the site(s) to verify that randomization/dispensing has been done accurately.
 |

A double-blinding technique with in-house blinding will be used. Metformin and placebo will be packaged identically so the blind is maintained. The participant, the investigator, and Sponsor personnel or delegate(s) who are involved in the study intervention administration or clinical evaluation of the participants are unaware of the intervention assignments.

Sponsor safety staff may unblind the intervention assignment for any participant with an SAE. If the SAE requires that an expedited regulatory report be sent to one or more regulatory agencies, a copy of the report, identifying the participant's intervention assignment, may be sent to investigators in accordance with local regulations and/or sponsor policy.

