#### **10.1.5. Committees Structure**

##### **10.1.5.1 Early Safety Data Committee**

- Participant safety will be continuously monitored by the Sponsor's internal committee, which includes safety signal detection at any time during the study
- In addition, an early aggregated safety data review will be performed, the goal of which is to allow for a cautious, stepwise approach to drug administration. An initial safety review for this study is planned for the first 30 participants (50% of participants) who are dosed and have provided safety data for 28 days after administration of Dose 1
- All safety data collected will be summarized and reviewed by the Sponsor's internal committee for agreement of next steps.
- In particular, data will be reviewed by the Sponsor for identification of the following events that would potentially contribute to a requirement to stop the study.
  - Any deaths, regardless of causality
  - Grade 3 AEs reported in more than 2 participants (see table in Appendix 4)
- Enrollment will be paused during the review. If a stopping rule is met, a decision will be made, based on the review, as to whether enrollment in the study will be allowed to resume.
- Case unblinding may be performed for above reviews if necessary.

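### Section 6.3 allows an expedited SAE report naming the participant's arm to go to investigators at the only centre, although the same section says they stay blinded throughout

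*Protocol*

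**What the plan says.** Section 6.3 makes four statements about who may know the allocation.

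- General rule: "Investigators will remain blinded to each participant's assigned study intervention throughout the course of the study". It adds that the participant, the investigator and the sponsor personnel "who are involved in the study intervention administration or clinical evaluation of the participants are unaware of the intervention assignments".
- Emergency code-break: "the investigator has the sole responsibility for determining if unblinding of a participants' intervention assignment is warranted".
- Sponsor access: "Sponsor safety staff may unblind the intervention assignment for any participant with an SAE".
- Reporting: "If the SAE requires that an expedited regulatory report be sent to one or more regulatory agencies", then "a copy of the report, identifying the participant's intervention assignment, may be sent to investigators in accordance with local regulations and/or sponsor policy".

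Three other places bear on this. Section 8 says that safety or laboratory findings capable of unblinding are withheld from blinded personnel until the study itself is unblinded. Section 10.4.4 says that the sponsor notifies the national agency, the ethics committees and the regional health authority of every suspected SAE within fifteen days, or seven if it was fatal or life-threatening, under current regulations. Section 10.1.5.1, on the sponsor's internal safety committee, says "Case unblinding may be performed for above reviews if necessary".

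**The concern.** The reporting sentence permits what the general rule excludes. A report that names the arm ends the investigator's blind for that participant. Nothing in Section 6.3 limits the copy to investigators who no longer assess that person.

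This matters because much of what happens after an SAE depends on investigator judgement. Stopping drug for adverse events (Section 7.1.1), rechallenge (7.1.3) and withdrawal (7.2) involve the investigator's discretion. Causality is assigned by the investigator and may be revised on follow-up information (10.4.3). Frailty measures are secondary endpoints at weeks 48, 96 and 144, and grip strength, walking speed and the physical performance battery depend on effort and on how the test is run. Adverse event incidence and severity are compared between arms (9.4.4). If allocation is known for some participants, these data are no longer collected blind for them.

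**Working it through.** No formula applies: the protocol gives no SAE rate, expedited-report rate or unblinding rate. The check sets the passages side by side.

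1. **Which sentence conflicts.** The blinding statement in 6.3 covers the participant, the investigator, and sponsor personnel involved in administration or clinical evaluation. Safety staff handling SAEs are not named, so their right to unblind contradicts nothing. The reporting sentence names investigators as recipients of an allocation-identifying document, and this meets the rule that investigators stay blinded head on.

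2. **Limits on disclosure.** The reporting sentence has three: the SAE must need an expedited regulatory report, sending is optional, and it follows local regulations and/or sponsor policy. It has no fourth limit excluding investigators who are still assessing the participant.

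3. **How tight the first limit is.** Section 8.5.4 speaks of SUSARs when it describes safety reports that investigators review and file. Section 6.3 does not use that term. Section 10.4.4 describes authority notification as covering suspected SAEs generally. That may be loose wording for suspected unexpected serious reactions, since it refers to current regulations, but it does not say so. As written, the class of events that opens the route is not clearly bounded.

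4. **Consistency with Section 8.** Section 8 withholds potentially unblinding safety results from blinded personnel, and an investigator is blinded under 6.3. A report that names the arm does more than risk unblinding. Section 8 states no exception for expedited reports.

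5. **Who receives the copy.** Section 4.1 describes a single-centre trial, so the recipients belong to the site that follows the participant. Section 7.1 asks that participants who stop drug be kept in the study for safety follow-up. A participant who has died or left the study has no later assessment to be affected.

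6. **Which data are exposed.** The intention-to-treat-exposed set (9.3) keeps observations made after discontinuation, so later frailty data stay in. Adverse events continue to be collected until the last visit (8.5.1). The primary endpoint comes from a methylation array (Section 10.2, Table 3), so a known allocation does not alter the reading. It could act only through decisions about staying on drug.

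**The case against.** The best defence is that the general rule already has exceptions in the same section, namely the emergency code-break and auditor access, and that the reporting sentence is one more. This carries some weight: the fault may be one of drafting rather than intent. It does not reconcile the text. The emergency route is the investigator's own decision for clinical need, and auditors do not assess participants. The reporting route is started by the sponsor, has no stated care need and reaches the assessors. It is not labelled an exception, and Section 8 has none that fits.

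Four stronger readings are tempting and are not supported:

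- **Any SAE leads to disclosure to the site.** The any-SAE wording applies only to sponsor safety staff. The copy to investigators is optional and tied to expedited reporting.
- **About 5 to 12 participants would be affected.** That range comes from 60 participants (Section 10.1.5.1 treats 30 as half) followed for 144/52.18 = 2.76 years, with an assumed 3 to 8 first SAEs per 100 person-years: 60 × (1 − exp(−0.03 × 2.76)) = 4.8 and 60 × (1 − exp(−0.08 × 2.76)) = 11.9. The rates are not in the documents. The result also counts people open to unblinding by sponsor staff, which is not disclosure to investigators.
- **The internal committee's case unblinding leaks to the site.** Section 10.1.5.1 is silent on this, and Section 8 points the other way.
- **Other participants' arms would be revealed.** Only the reported participant's arm is named. Guessing others from similar side effects is conjecture.

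It is also fair to say that the unseen local regulations or sponsor policy might prevent any such copy being sent. The protocol should then say so.

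**Conclusion.** The inconsistency is real and narrow. The reporting sentence in 6.3 permits disclosure to investigators that the general rule in 6.3 and the withholding rule in Section 8 do not allow, at a centre where the recipients may still be assessing the participant.

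Its numerical size cannot be given, because the documents state no rate for expedited reports or for copies sent. With about 30 evaluable participants per arm, a few disclosures could matter for the judgement-dependent outcomes: frailty tests, adverse event severity and causality, and discretionary discontinuation. For the primary methylation endpoint the effect is at most indirect. A participant who stops drug is still analysed in the intention-to-treat-exposed set.

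The conclusion assumes that the text is applied as written, that at least some reports concern participants still in follow-up, and that no unseen policy already provides blinded copies.

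**What to change.** Change the reporting sentence in Section 6.3 so that the allocation-identifying report goes only to the authorities and ethics committee that require it, and investigators receive a blinded copy unless local regulation requires otherwise. This also brings 6.3 into line with Section 8.

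Align Section 10.4.4 with Sections 6.3 and 8.5.4 on which events need expedited notification, so that the condition in 6.3 has a defined meaning.

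Leave unchanged the emergency code-break in 6.3, the sponsor safety staff's own access, and the internal committee's case unblinding in 10.1.5.1. None of these creates the conflict.

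The cost is a few sentences, plus a blinded and an unblinded version of each expedited report.

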#### 6.4. Study Intervention Compliance

When participants self-administer study intervention(s) at home, compliance with study intervention will be assessed at each visit. Direct questioning will assess compliance and counting returned tablets during the site visits and documented in the source documents and relevant form. Deviation(s) from the prescribed dosage regimen should be recorded.

A record of the number of tablets of metformin or placebo dispensed to and administered by each participant must be maintained and reconciled with study intervention and compliance records.

Intervention start and stop dates, including dates for intervention delays and/or dose reductions will also be recorded.

### 6.5. Dose Modification

This protocol allows some alteration from the currently outlined dosing schedule, but the maximum daily dose will not exceed.

If there are changes in the antiretroviral treatment, such as starting or stopping dolutegravir, the dose of metformin should be modified accordingly. If dolutegravir is initiated the dose of metformin should be reduced to 850 mg once a day. If dolutegravir is stopped, metformin dosing should be modified to 850 mg dose twice daily.

In those participants that experienced grade 2 gastrointestinal adverse events after metformin dose increase, dose of metformin will be reduced dose to 850 mg once daily.

In case a dose reduction is necessary due to renal impairment, the study intervention will be administered as follows:

